## Abstract

**Background:**

A new dashboard, the 360ºCHILD-profile, was developed to adopt personalized health care within preventive child health care. On this profile, holistic health data are visualized in a single image to provide parents, adolescents, and caregivers direct access to a manageable résumé of a child’s medical record. Theoretical ordering, conforming to “International Classification of Functioning, Disability and Health for Children and Youth”, guides clinical reasoning toward the biopsychosocial concept of health. It is yet unknown if and how this promising tool functions in practice, and a variety of feasibility questions must be addressed.

**Objective:**

This paper describes the design and methods of a feasibility randomized controlled trial (RCT), with the aim of evaluating the RCT’s feasibility (recruitment, response, measure completion, and intervention allocation) and 360ºCHILD-profile’s feasibility (usability and potential effectiveness).

**Methods:**

A pragmatic mixed methods study design was chosen, starting with an RCT to measure feasibility and health literacy in 2 parallel groups (1:1). Qualitative research will then be used to understand and explain quantitative findings and to explore the stakeholders' perspectives on the potential of the 360ºCHILD-profile. Participants will include child health care professionals (n≥30), parents (n≥30), and caregivers (n≥10) of children who experience developmental problems (age 0-16 years). Children will only be able to participate if they are older than 11 years (adolescents, n≥10). The 2 groups included in the study will receive standard care. The experimental group will additionally receive personalized 360ºCHILD-profiles.

**Results:**

After an intervention period of 6 months, quantitative outcomes will be measured, analyzed (descriptive feasibility statistics and preliminary between-group differences) and used to purposively sample for semistructured interviews.

**Conclusions:**

Study results will provide knowledge for building theory on the 360ºCHILD-profile and designing future (effect) studies.

**Trial Registration:**

Netherlands Trial Register NTR6909; https://www.trialregister.nl/trial/6731

**International Registered Report Identifier (IRRID):**

DERR1-10.2196/21942

## Introduction

To more effectively address the increasing burden of preventable chronic diseases, it is a prerequisite for current reactive health care (treatment after a diagnosis) to make the transition to personalized health care (PHC) [1]. According to Snyderman [2], PHC stands for a lifetime, holistic approach of proactively offering predictive, preventive, personalized, and participatory care. The different PHC concepts can and must be introduced in practice as soon as possible, but it appears to be a challenging task to effectuate such a new approach within health care [2,3].

Dutch preventive child health care (CHC), as part of public health, offers a unique platform to adopt PHC in the short term. CHC proactively monitors children’s development and health to detect early deviance from normal variance and diseases or symptoms which cannot yet be clustered to a diagnosis. To fully apply PHC within the preventive CHC approach, a shift is needed toward prediction and prevention in the very early stages of disease progression when symptoms may not even be present [4,5]. To perform early detection and act upon disease progression is not an easy task because health processes are complex. The biopsychosocial model of health shows that health is a result of lifelong, multidimensional interactions between many biological–genetic characteristics and environmental factors. Therefore, to predict and protect health, insight into a broad set of health determinants is required. Critical to implementation of PHC is thus the availability and accessibility of high-quality, relevant lifetime health data.

From birth on, CHC collects health data about the child and environment, which are stored in an electronic medical dossier (EMD). However, accessibility of data is profoundly hindered due to the actual structure of EMDs, and thus support for the complex clinical reasoning process is insufficient [6,7]. It is not possible to generate an adequate overview of registered data in coherence with the relevant theoretical concepts (ie, the biopsychosocial model) [8]. As a result, much of the CHC-data that are highly relevant to understanding the complex processes underlying health are not available within the timeframe of CHC visits or other consultations with caregivers and parents.

To address this problem, a 360ºCHILD-profile (Figure 1), which visualizes health information about the child and environment in a single digital image, has been originally developed and examined within daily practice of the Dutch CHC system [9].

Relevant CHC data, visualized on the 360ºCHILD-profile, are theoretically ordered according to the “International Classification of Functioning, Disability and Health for Children and Youth” (ICF-CY) [10]. The ICF-CY fits the CHC context and PHC concepts, as it is built on the integrated biopsychosocial approach of health and describes a broad variety of individual characteristics and environmental factors in concrete, neutral (if not positive) formulations [10]. The 360ºCHILD-profile was developed as a dashboard that provides a quick, systemic, and comprehensible representation of a child’s individually unique set of health determinants (protective and risk factors).

The goal of the 360ºCHILD-profile is to provide direct access to a manageable résumé of holistic health information stored in the EMD to CHC professionals, parents, and adolescents, and to naturally guide thought processes in coherence with the chosen theoretical perspective (PHC). This dashboard supports health literacy in a way that can empower parents and adolescents to cocreate personalized plans for managing their (children’s) health, in partnership with caregivers [11,12]*.*

From the very start of the 360ºCHILD-profile’s development and research project (2012), parents, adolescents, and CHC professionals have been actively involved. Formal ideas for designing the profile’s first drafts were generated, and pilot studies showed positive reactions of stakeholders for the comprehensibility, relevance, and acceptability of the design [9]. Promising results were generated in another study related to the 360ºCHILD-profile’s reliability and validity when used by CHC medical doctors to assess child functioning [13]. In 2018, data visualization designers and researchers used their expertise and gained input from stakeholders on CHC context, usability, and user experience to redesign the 360ºCHILD-profile [9].

The current state of this newly developed 360ºCHILD-profile offers a promising, online dashboard that is ready to be introduced into CHC practice. If and how it will actually function within daily practice is yet unknown, and it is foreseen that the evaluation of effectiveness in the multidisciplinary and preventive CHC context will be complex. Therefore, a pragmatic feasibility RCT will be performed to refine our practice-derived theory on the 360ºCHILD-profile’s feasibility and potential effectiveness and to build a rationale for designing future (effect) studies (including outcome measures and sample size calculations) [14,15]. The aim of this paper is to describe the design and methods of this study that will be performed within CHC.

**Figure 1 figure1:**
[figure not shown]
The 360°CHILD-profile: representation of a child’s health information available in the CHC electronic medical dossier, based on the "International Classification of Functioning, Disability and Health for Children and Youth” [10]. Child’s name, gender, and age appear in the center; the most recently acquired data about the child’s body functions and structures in physical and mental aspects appear in the blue area; and information on activities and participation appear in the yellow area. Data about genetic predisposition and history (medical, developmental, and life events) are listed in the left column, and information about environmental factors are in the right column. On top of the 360ºCHILD-profile, a timeline is provided with bullet points at which ages the child visited CHC, and a CHC and a 360ºCHILD-profile (snap-shot) is generated. At the bottom of the 360ºCHILD-profile, conclusions and advice from the most recent CHC visit are presented. CHC: child health care.

## Methods

### Study Design

For this pragmatic feasibility RCT, a sequential mixed methods design was chosen. First, quantitative research will be performed. Within the limitations of a feasibility study [16], an RCT will be executed with 2 parallel groups (experimental and control). Qualitative research will then be performed to understand and explain the quantitative findings and to explore the 360ºCHILD-profile’s potential benefit in CHC practice [17-19]. The study objectives will be to evaluate 2 types of feasibility: that of the 360ºCHILD-profile and that of the RCT.

(1) The 360ºCHILD-profile feasibility evaluation will include the following: usability, including the frequency and profundity of 360ºCHILD-profile use during contacts between CHC professionals, parents, adolescents, and other caregivers; and the perspective of parents, adolescents, CHC professionals, and other caregivers on quantitative findings, requirements for the 360ºCHILD-profile’s use within CHC, and potential benefit and effectiveness.(2) The RCT feasibility evaluation will include the following: recruitment, retention, and response rates; acceptance of and compliance to allocated interventions; measurement completion and protocol deviations; health literacy measurement, including the variance of parent’s satisfaction on health literacy in the total and in each separate group, and a preliminary estimation of the between-group differences; the perspective of parents, adolescents, and CHC professionals on hindering and promoting factors for recruitment, retention, and response rates, acceptance and compliance to allocated intervention, measurement completion, and preliminary differences on health literacy.

### Study Population and Sample Size

The study population will mainly consist of parents and CHC professionals (nurses and medical doctors) who are involved in the care of the parent’s child (age 0-16 years) experiencing emerging problems. Adolescents (age >11 years) and other involved caregivers can also be included as participants, but children under the age of 12 years will not themselves participate. If parents or adolescents cannot comprehend the written health information (due to a language barrier or other reasons), they will not be included in this study.

For the quantitative phase, we aim to recruit 30 parents, 30 CHC professionals, 10 adolescents, and 10 other caregivers. For feasibility studies, in which outcome parameters like recruitment, response rates, and variance in the outcomes of questionnaires (SD) are measured, a sample size of 60-70 participants is justified [16,20,21]. For qualitative research with purposive sampling, it is estimated that saturation will be reached after including 20-30 participants (7-10 participants per target population; ie, parents and CHC professionals) [19,22].

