#### RCT Feasibility

Evaluation of the RCT feasibility will occur in both group and is described in this section.

The quantitative measurements will include the following: recruitment rate (the percentages of volunteers versus invited and eligible participants); retention rate (the percentage of participants completing the study versus the participants that started); response rates (the percentages of participants per discipline who filled in and validated the questionnaire versus the number of participants who were requested); compliance to allocated intervention (the percentage of CHC professionals in the experimental group who used the 360ºCHILD-profile during a CHC visit); measure completion (the percentages of completed measures versus incomplete measures and description of missing data); protocol deviations (the description of problems encountered and eventual adaptations to the protocol for properly addressing these problems); health literacy.

Health literacy will be evaluated using the validated Dutch version of the Consumer Quality Index (CQI). The CQI is based on the Consumer Assessment of Healthcare Providers and Systems (CAHPS) and is applicable for parents of children aged 0-18 year who visit CHC [29]. The validated CQI includes questions about accessibility, ability to understand, completeness and applicability of received care, and health information and advice, with answer options on a 2-, 3-, or 4-point scale (subscale reliability: Cronbach α=.75-.82) [30]. Additionally, relevant questions from “Supplemental Items for the CAHPS on Health Information Technology” were translated from English to Dutch and incorporated into the CQI questionnaire [31]. The research team developed additional questions to ensure measurement of all dimensions of the construct’s “access to healthcare and health information” [32]. The dimensions we indicated as relevant for the CHC context and this study are availability, accommodation, accessibility, and acceptability. Affordability is not relevant in this context because CHC care is offered for free to all children and parents. This set of additional questions (n=6) with answers options on a 5-point scale will be used for the first time, and no information on the diagnostic parameters is available yet.

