From a pragmatic viewpoint, we searched for design options that fit current research questions and CHC context. A mixed methods design with a sequential explanatory (quantitative–qualitative) setup was chosen to enable testing our a priori, practice-based hypotheses and to give voice to parents, adolescents, and caregivers to refine theory. The pragmatic approach of the feasibility RCT enables the execution of a randomized trial within the preventive and multidisciplinary field of work and generation of results that fit this context [17]. The investment of time by CHC professionals is limited as much as possible; only a short training period is needed, each professional will need to recruit only 1-2 parent(s), and professionals are left close to daily practice during the “intervention” period (care as usual). Furthermore, CHC professionals in the experimental group do not have to drastically change their working method; they will present the personalized profile to parents and adolescents, but after that, all participants are free in choosing how (often) to use it. The between-group difference might seem rather subtle, but we expect it will have substantial impact. Our hypothesis is that the availability of the dashboard will automatically lead to efficiency (there is less wasting of time to search for data in the EMD and better quality of health literacy and early prevention of disease progression). Moreover, we expect that the theoretical structure of the profile will intuitively guide clinical reasoning in line with the context of CHC and PHC.

Information bias will be reduced by the centralized randomization, blinding of researchers for randomization, and keeping participants unaware of the detailed study aims.

Children and their parents have been chosen as the level of randomization (and not CHC professionals) to avoid bias due to differences in professionals’ working methods, characteristics, and level of experience. Contamination is avoided by virtue of the fact that, for CHC professionals in the control group, it is not possible to obtain an overview of the holistic health data from the EMD, as it is simply not available.

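### The 60-70 participants cited for estimating a questionnaire SD are not reached for health literacy, which is measured in a target of 30 parents, about 15 per group

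*Protocol article*

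**What the plan says.** Under Study Population and Sample Size, the article sets the targets for the quantitative phase: "we aim to recruit 30 parents, 30 CHC professionals, 10 adolescents, and 10 other caregivers". The next sentence justifies the size for feasibility studies in general. It names recruitment, response rates and questionnaire spread as the kind of outcome meant, and says that where "variance in the outcomes of questionnaires (SD) are measured, a sample size of 60-70 participants is justified". Support is by citation only. No significance level, power, SD, interval width or attrition allowance is given, and the article does not say which respondents make up the 60-70.

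The Abstract words the same targets as minimums: "Participants will include child health care professionals (n≥30), parents (n≥30), and caregivers (n≥10", with adolescents also at 10 or more.

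The Study Design section makes one questionnaire variance an objective: the "variance of parent’s satisfaction on health literacy in the total and in each separate group", together with a preliminary estimate of the difference between groups. The RCT Feasibility section names the instrument, the Consumer Quality Index (CQI), which "is applicable for parents of children aged 0-18 year who visit CHC". Parents are randomized 1:1 (Randomization and Concealed Allocation). Quantitative Outcome Data plans a mean, SD and CI for the total sample and for each group, and a between-group difference with a 95% CI. The Introduction gives the purpose: "to build a rationale for designing future (effect) studies (including outcome measures and sample size calculations".

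**The concern.** The justification names the SD of questionnaires as one of the outcomes that 60-70 participants serve. The only questionnaire SD that the article makes an objective is that of parents' health literacy, and the parent target is half of 60. Answers from professionals or other caregivers carry no information about the spread of a parent questionnaire, so they cannot make up the shortfall.

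This matters because the feasibility estimates are meant to inform the sample size of a later effect study. Required size scales with the square of the SD, so uncertainty in the SD carries over directly. A reader who takes 60-70 as the basis of the health-literacy SD would think it better determined than it will be.

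**Working it through.** **Inputs.** Targets by respondent type: 30, 30, 10 and 10 (Study Population and Sample Size). Allocation 1:1 among parents (Randomization and Concealed Allocation). Health literacy measured in parents (Study Design, RCT Feasibility). Normality of the score is my assumption.

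**Step 1: can the 60-70 be reproduced?** Not by formula, since the article gives no inputs. From the targets:
- parents + professionals: 30 + 30 = 60
- plus one group of 10: 30 + 30 + 10 = 70
- all four types: 30 + 30 + 10 + 10 = 80
- parents alone: 30, or 30 / 2 = 15 per group

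Only sums across types give 60 or 70. Even if adolescents' answers were counted with parents', which the article does not say, the total would be 30 + 10 = 40.

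**Step 2: precision of the SD.** The 95% limits for the true SD, as multiples of the estimate, are √(df/χ²(0.975, df)) and √(df/χ²(0.025, df)), with df = n − 1.

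| n | df | Lower | Upper |
|---|---|---|---|
| 15 (one group) | 14 | √(14/26.12) = 0.73 | √(14/5.63) = 1.58 |
| 30 (all parents) | 29 | √(29/45.72) = 0.80 | √(29/16.05) = 1.34 |
| 60 | 59 | √(59/82.12) = 0.85 | √(59/39.66) = 1.22 |
| 70 | 69 | √(69/93.86) = 0.86 | √(69/47.92) = 1.20 |

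Using the pooled within-group SD from 30 parents (28 df) hardly changes the result: 0.79-1.35.

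**Step 3: precision of the difference.** The 95% half-width in SD units is t(0.975, N − 2) × √(4/N), for N parents split equally.
- N = 30: 2.048 × 0.365 = 0.75
- N = 60: 2.002 × 0.258 = 0.52
- N = 70: 1.995 × 0.239 = 0.48

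**Step 4: what the SD uncertainty means for a later sample size.** Squaring the upper limit gives 1.34² ≈ 1.8 with 30 parents and 1.58² ≈ 2.5 with one group of 15, against 1.20² to 1.22² ≈ 1.4-1.5 with 60-70.

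**Step 5: sensitivity to the number of parents.** The article states no loss rate. With an assumed 10% or 20% loss, 27 or 24 parents remain. The SD limits become 0.79-1.37 or 0.78-1.40, and the half-width 0.79 or 0.85 SD. In the other direction, the Discussion has each professional recruiting one or two parents. Thirty professionals recruiting two each would give 60 parents, and the n = 60 figures would then apply. The stated aim is nevertheless 30.

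**The case against.** The sentence on 60-70 is general and lists several outcomes. Recruitment, retention and response rates do span respondent types, so an overall count may be reasonable for them, and nothing here shows otherwise. That the figure is a sum across types is inferred, and all four targets add to 80. The cited sources are not at hand, so what they mean by 60-70 cannot be checked. Thirty parents is a minimum in the Abstract. All of this stands, and it limits the point to the health-literacy estimates. It does not make 60-70 apply to them, because no single respondent type has a target of 60.

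Three stronger readings are tempting and are not supported:

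- *That a promised precision is not delivered.* The article promises none. The interval widths above are this review's calculation, and the planned CIs will reflect the number of parents actually observed.
- *That the trial is underpowered to detect an effect its authors call subtle.* In the Discussion that remark concerns how little care differs between the groups, and the same sentence expects a substantial impact. No effect size, significance level or power is given, so there is no power claim to refute.
- *That a hypothesis test is planned.* The Discussion says the mixed methods design "was chosen to enable testing our a priori, practice-based hypotheses", but the clause explains the choice of the whole design. The Statistical Analysis section plans preliminary estimates with 95% CIs and no significance test. At most the word could be aligned with that plan.

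Nor does the article say that the next trial will be sized from the SD point estimate or from the observed difference. How that later trial uses these results is for its own protocol.

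**Conclusion.** The point holds for the health-literacy SD and the between-group difference. The article cites 60-70 participants for an SD of this kind, and its parent target supplies 30, about 15 per group before loss. At that size the upper 95% limit for the SD lies about 34% above the estimate overall and 58% above it per group, against 20-22% with 60-70. The difference is estimated to within about ±0.75 SD, against ±0.48 to ±0.52 SD. These figures assume normal scores, equal groups and exactly 30 parents. Losses would widen them and recruitment beyond the minimum would narrow them. A feasibility sample of 30 parents is not itself an error. The fault is that the printed justification does not fit the outcome it names.

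**What to change.** Restate the justification by outcome in Study Population and Sample Size:

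- Keep 60-70 only for the outcomes it is meant to serve, and say which respondents make it up.
- Do not apply it to the health-literacy SD or the between-group difference. State that these rest on about 30 parents, roughly 15 per group before loss.
- Give the expected precision, with the normality assumption: 95% limits of about 0.80-1.34 times the SD overall and 0.73-1.58 per group, and a half-width of about 0.75 SD for the difference.
- If 60-70 was intended for this SD, the parent target has to change instead.

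As an optional wording point, bring the Discussion's reference to testing into line with the estimation plan in the Statistical Analysis section.

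The restatement is wording only and needs no extra participants or measurements. Its cost is that a stated figure becomes less favourable. Raising the parent target would mean more recruitment.
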